### Actual intervention

Participants in both the intervention and control groups can lead a normal life, with no particular restrictions or changes in daily care, which will continue in both study groups.

Interventions will be conducted according to the results of individual test results, baseline questionnaire data, drinking calendar records, and health guidance materials, including conventional teaching materials [33]. The main contents of the health guidance materials are as follows:Alcohol action (disinhibition/relaxation, sedation/anesthesia, blood alcohol concentration, and drunken stages and symptoms)Mechanism of comfort and discomfort associated with drinking (relationship with neurotransmitters in the brain reward system, action of alcohol-metabolizing enzymes, harmfulness of acetaldehyde)Alcohol constitution (what type of constitution from A to E, characteristics, and comments by constitution type)Drinking habit screening test (AUDIT-C: ≥6 points for males, ≥4 points for females) and feedback that continuing the current drinking habits may eventually affect the mind and bodyDrinking amount ranking based on the current drinking amount (national standard table of drinking for general adult males and females)Generally appropriate amount of alcohol: two drinks for males (20 g of pure alcohol) or less on average per day, one drink (10 g of pure alcohol) or less for femalesThe number of people who are vulnerable to alcohol, who are older, and who have a red face when drinking alcohol is even lessGenerally inappropriate drinking (drinking while pregnant/lactating, driving a car (including a bicycle), minor, illnesses, or medications affected by drinking)Drinking with a high risk for lifestyle-related diseases: four drinks for males on average per day (40 g of pure alcohol) or above, two drinks for females (20 g of pure alcohol) or aboveBinge drinking: within 2 h, five drinks for males (50 g of pure alcohol) or more, four drinks for females (40 g of pure alcohol) or moreInformation from recent studies: zero daily drinking may be desirableParticipants’ intentions regarding drinking behavior and drinking habits (continuing or reviewing the current drinking habits is better)Participants’ opinion about the advantages and disadvantages of drinking alcoholReview on how to drink, the possible goal, and the concrete methodExamples of self-monitoring: proposal for continuing the drinking diary and drinking calendar recording

During the intervention, the intervening researcher confirms the participants’ perceptions of drinking behavior and drinking amount, their intention to review their habits, and the content they intend to change, and respects the participants’ ingenuity in drinking methods and goal setting.

The intervention time is approximately 30 min as a guide, but it can be extended to 1 h to answer questions, share information with each other, and communicate. At the end of the intervention, the participants are told that they can contact the intervening researcher via e-mail for any questions or consultations, and they can respond to via e-mail as well, as needed. If an interview is requested after the intervention, we will set up an interview at the end of the half-year survey and only follow them up by e-mail. Given that measures against COVID-19 are required during the planning and implementation of this study, the application Zoom was used as the intervention method in accordance with the participants’ wishes and place of residence (during homecoming, etc.). Thus, the interview is conducted online or face-to-face. After the registration of participants had started, the progress was reported and the status was confirmed at a joint researcher’s meeting once a month.

### Conventional teaching materials

In the control group, the conventional teaching materials (alcohol handbook for university students) [33] will be handed over to the participants during the consent procedure and requested to be read. The survey will only be conducted for half a year by providing the conventional materials.

The main contents of the conventional materials are also included in the abovementioned test result report and health guidance materials for intervention. Although some descriptions are duplicated, the main contents are as follows:A recall of experiences such as the loss of a child or parent resulting from a fatal accident or illness caused by drinking alcohol, or a dangerous experienceCurrent drinking style of university students (results of the drinking attitude survey)Conversion of the amount of alcohol consumed on the day of drinking according to a conversion table and checking of the current amount of alcohol consumed by using the alcohol consumption ranking table (male, female)Stage from tipsy to death resulting from acute alcohol intoxicationBinge drinkingChecking, defining, and coping with alcohol and harassmentSpecific examples of ideas for keeping tipsy at drinking partiesKnowledge of alcohol (alcohol-related problems: violence, depression, sleep-related problems, family and workplace problems, mental and physical illnesses caused by alcohol, etc.)

## Ethics and dissemination

This research began in July 2021, with the approval of the Institutional Review Board of Medical Doctors, University of Tsukuba (Human Genome/Gene Analysis Research). If there are any changes in the research protocol, the principal researcher will apply to the Institutional Review Board of Medical Doctors, University of Tsukuba (Human Genome/Gene Analysis Research) for approval.

The researcher strictly manages the correspondence table that collates the participants with the ID number, and the data are managed so that the participant’s name and the information on the genotype constitution heard are not directly linked. Data input and analysis are mainly performed by the first author using a computer with security measures, and data collection and analysis results are regularly checked with collaborators.

This research was conducted in compliance with the “Ethical Guidelines for Human Genome/Gene Analysis Research” established by the Ministry of Health, Labor, and Welfare. Registration for the UMIN clinical trial was completed on June 1, 2021. The results of this research will be published in peer-reviewed academic journals and at internal and international academic conferences.

## Monitoring

Although this study is an intervention study, it is an educational intervention, and saliva testing is not considered invasive. Therefore, there is no data monitoring. To maintain compliance, we collaborate with researchers to attend monthly online meetings to share progress, data collection, and intermediate analysis results and discuss issues. Regarding the decision to suspend the recruitment of participants, the progress of the trial will be shared at the meeting, and if there is no problem in conducting the exam, the recruitment will be suspended when the number of subjects to be analyzed reaches the target. This research is subject to progress checks and audits every 6 months by the Institutional Review Board, and the person in charge of the audit is independent of this study.

## Risks, burdens, and benefits

Participation in this study is considered of little risk. However, 6 months of cooperation surveys, answering questionnaires, and receiving interventions are a small burden. As a benefit of participation, knowing the genetic predisposition of alcohol-metabolizing enzymes can lead to better management of drinking behaviors and reduced risks associated with drinking. On the contrary, information about the health risks associated with drinking may lead to participant anxiety. We will provide contact information for follow-up consultation in the case of mental burden. In the unlikely occurrence of an adverse event, participants will be instructed to contact the researcher, who will notify the responsible researcher’s doctor and take appropriate action, and will report to the department of the Institutional Review Board of Medical Doctors, University of Tsukuba (Human Genome/Gene Analysis Research) as necessary.

## Discussion

Information on the genetic function and constitution of alcohol-metabolizing enzymes provided individually by the study’s intervention may lead to a transition to a period of interest, such as a partial review of drinking methods, from indifference that participants perceive alcohol drinking as personal and objective information rather than general health information and are not aware of alcohol or hazardous drinking. At least in Japan, where the proportion of low *ALDH2* activity (a genetic component peculiar to East Asians) is high [1, 2], genetic polymorphism information of alcohol-metabolizing enzymes may be utilized for health management and risk prevention. Particularly, the prevention of lifestyle-related diseases for each *ALDH2* polymorphism has been elucidated as follows [34]: *ALDH2 * 2* allelic carriers have a higher risk of carcinogenesis than non-*ALDH2 * 2* but are less likely to increase blood pressure and have relatively lower serum liver transaminase (AST: aspartate transaminase, ALT: alanine transaminase, GGT: γ-glutamyl transpeptidase) and uric acid levels.

Moreover, *ALDH2 * 2* allelic carriers may not have an opportunity to monitor their drinking habits [34]. Therefore, if a genetic predisposition delays the detection of abnormal biological indicators even with excessive drinking, detailed information on gene polymorphisms of alcohol-metabolizing enzymes in patients with lifestyle-related diseases may serve as an indicator to consider their drinking habits.

As previously mentioned, carriers of *alcohol dehydrogenase 1B* (*ADH1B * 1 / * 1* genotype) have been reported to be at an increased risk of alcohol dependence [2], as well as an increased risk of head and neck cancer caused by alcohol consumption [6–8]. Previous studies conducted interventions involving only *ALDH2* genotype information [13, 19]. In this study, we propose a novel brief intervention that classifies the types of *ALDH2* and *ADH1B* gene polymorphisms into five combinations in an easily comprehensible manner. However, the effectiveness of health guidance using the information on *ALDH2* and *ADH1B* gene polymorphisms needs to be verified by increasing the sample size. Regarding the strength of this study, we will investigate the intervention effects of new efforts using the method of randomized controlled trials.

As mentioned in the introduction, a randomized controlled trial using the genetic information of the alcohol-metabolizing enzyme *ALDH2* validated the effect 30 days after providing Internet-based *ALDH2* genotype and health risk information [13]. In this previous study, the frequency and amount of drinking were significantly reduced after 30 days in the feedback group with low *ALDH2* activity. However, their follow-up period was 30 days, which is shorter than 6 months (maintenance period) [28], for behavioral habituation and maintenance. Therefore, the strength of the current study is the investigation of the intervention effect until 6 months (maintenance period) [28], which is the standard duration for behavioral habituation, and verification of its long-term efficacy.

Conversely, one limitation of this study is that when students agree to participate, they already know if they are in the group to be tested or not; hence, they cannot be blinded. Regarding the primary outcome measure, the average drinking amount on the drinking day is limited to the calculation of the amount of drink with an unknown alcohol concentration or amount. In addition, given that this research deals with genetic information, we need to evaluate the intervention effect by interviewing each participant. We also need to examine a system that can be useful for enrolling large groups, such as university students.

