## Methods

### Overview of the study design

The study population is divided into two groups: the intervention group (which performs individual interventions for drinking habits, including the results and points to note concerning genotypes determined using saliva) and the control group (which has no constitutional examination during the study period, providing only conventional teaching materials). This study is an open-label, randomized controlled trial. We chose an open-label trial because participants can be distinguished between the intervention group, who undergoes the test of genotypes at baseline, and the control group, who wishes to test for genotype after 6 months of study. In principle, the outcome evaluator does not provide interventional care, and only the outcome evaluator is blinded.

Figure 1 shows the study flow chart, and Table 1 lists the components of the five genotypes of alcohol-metabolizing enzymes and the major health risks.

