### Screening and informed consent

Simultaneously, as the consent procedure, a self-administered questionnaire survey of baseline data are conducted, and the explainer confirmed the drinking status and average drinking amount during questionnaire collection. The procedure for explanation and consent is mainly conducted by the first author. With written consent, the intervention group is tested for alcohol-metabolizing enzyme genotype using saliva. The explainer collect and mail the sample to the testing institution on the day of the test. On the consent form, participants will be asked if they agree to the use of their data, should they choose to withdraw from the trial. Participants will also be asked for permission by the research team to share relevant data with people from the universities participating in the study or, if necessary, from regulatory agencies. If the consent and permission are confirmed, the data can be used and shared. This study does not include collecting biological specimens for storage.

During the time of study planning and implementation, measures against coronavirus disease 2019 (COVID-19) are required. Informed consent is supposedly obtained in person; however, depending on the participant’s wishes and place of residence (during homecoming, etc.), explanation, consent, and inspection procedures are performed online and by mail, as necessary.

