### Randomization

In randomization, we simply used a computer-generated random number table, collate participants with anonymizing identification numbers, and assign them to the intervention group or the control group (100 participants per group). The first author mainly marked the random number table as the identification number of the intervention group before the start of recruitment and assigned it in the order of registration depending on the presence or absence of the mark.

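### Allocation is not concealed from the main recruiter or from participants at consent, and the stated evaluator blinding conflicts with how outcomes are collected and analysed

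*Protocol article*

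**What the plan says.** All places are in the protocol article.

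- **Making the list (Randomization).** "The first author mainly marked the random number table as the identification number of the intervention group before the start of recruitment", and then "assigned it in the order of registration depending on the presence or absence of the mark".
- **Recruiting and consenting.** Recruitment says that candidates are contacted by e-mail, mainly by the first author. Screening and informed consent adds: "The procedure for explanation and consent is mainly conducted by the first author".
- **Timing of baseline (Screening and informed consent).** "Simultaneously, as the consent procedure, a self-administered questionnaire survey of baseline data are conducted". The person giving the explanation also confirms the participant's average drinking when the questionnaire is collected.
- **Knowledge of arm (Discussion, limitations).** "when students agree to participate, they already know if they are in the group to be tested or not". Conventional teaching materials adds that controls receive their handbook during the consent procedure.
- **Blinding (Overview of the study design).** The trial is open-label, but, with the qualifier that this holds in principle, "only the outcome evaluator is blinded".
- **Handling of outcomes.** The primary outcome is self-reported drinking, by questionnaire and drinking calendar (Primary outcome measures). Replies are requested by e-mail, mainly by the first author (Measures). "Data input and analysis are mainly performed by the first author" (Ethics and dissemination).
- **Meetings (Monitoring).** Monthly meetings "share progress, data collection, and intermediate analysis results".

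**The concern.** Concealment and blinding are separate protections. An open-label trial gives up participant blinding after assignment. It can still keep the next assignment hidden until the participant has consented, been found eligible and given baseline data. This plan gives up both, and the limitations paragraph admits only the first.

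Two routes to bias follow.

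1. **Selective enrolment.** The genotype test is an evident attraction of the trial, and controls wait 6 months for it. People who learn they would be controls may decline, and those who remain may differ in motivation. The person who can foresee the arm also explains the trial and checks drinking amount, which is the eligibility variable.
2. **Arm-dependent baseline answers.** Baseline drinking may be reported by someone who already knows the arm. The analysis compares change from that baseline between groups, so a distorted baseline enters the primary comparison directly.

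The blinding statement adds a reporting problem. A reader would credit the trial with an independent assessment that the rest of the text does not describe. The Discussion presents the randomised design as the study's strength, so what weakens the randomisation should be stated correctly.

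**Working it through.** **Step 1. Who knows the arm, and when.**

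| Moment | Who acts | Arm known? | Section |
|---|---|---|---|
| List marked | Mainly first author | Whole sequence | Randomization |
| Candidate contacted | Mainly first author | Next arm readable from the marked list | Recruitment; Randomization |
| Explanation and consent | Mainly first author | Participant knows on agreeing | Screening and informed consent; Discussion |
| Baseline questionnaire and drinking check | Participant; explainer | Same occasion as consent | Screening and informed consent |
| Follow-up by e-mail | Participant; mainly first author | Yes | Measures |
| Data entry and analysis | Mainly first author | Yes, from the marked list | Ethics and dissemination |

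The table has no step at which consent, eligibility and baseline are complete while the arm is still unknown to both the recruiter and the participant. That is what concealment requires.

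**Step 2. Whether identification numbers restore blinding.** They do not. The marks that define the intervention group are on those numbers. The first follow-up is also timed differently: 1 month after the intervention in one arm and 1 month after baseline in the other (Abstract, Methods). The exclusion rule under Statistical analysis is arm-specific too.

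**Step 3. What the planned 0.2 means.** The documents give no figure for bias, and the only effect figure is the 0.2 under Sample size. With alpha 0.05 (two-sided for the t-tests), power 0.80 and exact noncentral distributions:

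- two-group F test with f = 0.2 (equivalent to d = 0.4): N = 199, matching the stated 199;
- paired t-test with dz = 0.2: N = 199, also matching;
- two-sample t-test with d = 0.2: 394 per arm, 788 in total, not matching.

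The 0.2 is therefore not a between-arm difference of 0.2 SD, and a bias in SD units cannot be divided by it.

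**Step 4. Illustration of consequence (bias values assumed).** With n = 100 per arm, no true effect and a between-arm bias of b SD in the analysed outcome, the two-sample t statistic has

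- degrees of freedom 2 × 100 − 2 = 198;
- noncentrality b × √(100/2) = 7.07b;
- rejection probability P(|t| > critical value) under that noncentral t.

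| Assumed bias b (SD) | Noncentrality | False-positive rate at nominal two-sided 5% |
|---|---|---|
| 0.05 | 0.35 | 6.4% |
| 0.10 | 0.71 | 10.8% |
| 0.15 | 1.06 | 18.4% |
| 0.20 | 1.41 | 29.1% |

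A larger sample would not remove this bias. For a fixed b, the noncentrality grows with n.

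**The case against.** **Roles are qualified.** Marking the list, contact, consent, collection and analysis are each described as mainly the first author's work, so others may do part of it. Recruitment is by poster and referral, and assignment follows registration order; the text does not show the recruiter choosing whom to approach. This stands against any claim that every allocation was foreseeable. It does not restore concealment, because no independent list holder is described and participants know their arm on agreeing.

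**Baseline is simultaneous with consent.** That the arm is known before the baseline answers is an inference. The text supports knowledge at agreement, with baseline on the same occasion.

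**Evaluator blinding.** A reader might infer that no blinded evaluator exists. The documents do not go that far. The statement is qualified, it separates the evaluator from giving the intervention, and collaborators regularly check results. What stands is the conflict with the other sections: no separate evaluator is identified, and blinding an evaluator does little for self-reports by participants who know their arm. The intervening nurse is not identified as the first author, so that link should not be drawn.

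**Size.** A reader might assume that 15% of control candidates decline and differ by 0.5 SD, giving 0.15 × 0.5 = 0.075 SD, and set that against 0.2 to get 38%. This is not supportable. Both inputs are assumptions. On the two-group reading of the sample size the share would be 0.075/0.4 = 19%, and on the paired reading the scales are not comparable. A stable difference in level at entry would also partly cancel in the comparison of changes. Arm-dependent baseline reporting would not cancel, because it alters the change itself.

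**Incentive to decline.** It is softened because controls are offered the test after 6 months, followed by the intervention if they request it.

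**Monthly meetings.** The text does not say that the intermediate results are split by arm.

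**Conclusion.** The concern holds in this form. Allocation is not concealed: the main recruiter marked the sequence, and participants know their group when they agree, on the occasion when baseline is taken. Enrolment and baseline drinking reports can therefore depend on arm, and the stated limitation does not cover this. Separately, the evaluator-blinding statement conflicts with Measures, Primary outcome measures, and Ethics and dissemination.

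The documents show exposure to bias, not that bias occurred or in which direction. Its size cannot be derived from them. The range of about 6% to 29% rests on an assumed bias of 0.05 to 0.20 SD, 100 analysed per arm, no true effect and a two-sided 5% t-test. The point should be fixed because it bears on the validity of the main comparison and because the text describes a protection it does not show.

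**What to change.** **For participants not yet enrolled**

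1. Discard the unused part of the marked sequence and regenerate it. Moving the present list to someone else is not enough, because the first author marked it. A collaborator who does not recruit should generate and hold the new one.
2. Complete consent, eligibility and the baseline questionnaire first. Only then release the arm, together with arm-specific material such as the control handbook and the saliva kit.

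**For the whole trial**

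3. Replace the evaluator-blinding statement with one saying that outcomes are unblinded self-reports. Alternatively, have a collaborator without the key run the between-group analysis on a dataset with new identification numbers and arms coded X and Y. Fields that reveal the arm, such as survey timing, must be withheld.
4. Keep between-arm outcome results out of the monthly meetings until follow-up ends.
5. Report allocation as unconcealed for those enrolled before the change. Add a descriptive comparison of results before and after it. With 200 participants in total this has low power and cannot rule bias out.

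**Cost.** A short amendment, a change in task order and a slight delay before participants learn their arm. It assumes that a non-recruiting collaborator is available; the article mentions collaborators but does not describe their duties in detail. Enrolment began in July 2021 and was planned to end in March 2023, so items 1 and 2 protect only those still to be enrolled.
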